# Assessment of primary endpoint

Specification of parameter

- Number and proportion of patients with at least one observed or self-reported adverse event (definition below)

Methods of data collection

Data on the occurrence of adverse events (severity, seriousness, causality), concomitant illnesses and concomitant drugs will be collected through direct continuous active clinical surveillance (including laboratory results) of all study subjects. All children will be examined by the responsible study physician at D0, D1, D2, D3, D7, D14 and D28.

# Assessment of secondary endpoints

Specification of parameters

- Number and proportion of patients with at least one serious adverse event:
  1. acute haemolysis (definition: haemoglobin  5 g/dl and haematocrit  15%, or received blood transfusion according to clinical judgement of study physician)
  2. Other serious adverse events (definition below)
- ACPR will be determined according to the standard WHO protocol (WHO 2003)
- Clinical and parasitological failure rates on day 3, 7, 14 and 28 will be determined according to the standard WHO protocol (WHO 2003)
- Time between inclusion and disappearance of fever
- Time between inclusion and clearance of parasites
- Change in the haematocrit after 2, 3, 7, 14 days and 28 days compared to baseline

Methods of data collection

The following laboratory methods will be employed:

Haematocrit will be measured with a centrifuge. Parasites will be diagnosed with standard techniques by light microscopy. Differentiation of recrudescences from new infections will be achieved by comparing PCR-generated *msp1* and *msp2* genotype patterns in matched pairs of isolates obtained on admission and precisely on the day of reappearance of parasitaemia.

Adverse event (AE) definition

The term “adverse event” covers any sign, symptom, syndrome, illness that appears or worsens in a subject during the period of observation in the clinical trial and that may impair the well-being of the subject. The term also covers laboratory findings or results of other diagnostic procedures that are considered to be clinically relevant.

No causal relationship with the study medication is implied by the use of the term “adverse event”. Adverse events fall into the categories non-serious and serious.

Serious adverse event (SAE) definition (GCP)

A serious adverse event is defined as any untoward medical occurrence at any dose:

(1) results in death (2) is life-threatening (3) requires inpatient hospitalisation or prolongation of existing hospitalisation (4) results in persistent or significant disability/incapacity (5) is a congenital anomaly / birth defect
(“Life-threatening” refers to an event in which the patient was at risk of death at the time of the event; it does not refer to an event which hypothetically might have caused death if it was more severe.)

Classification of severity

Mild: The adverse event does not interfere with the routine activities. The patient may experience slight discomfort.

Moderate: The adverse event interferes with routine activities. The patient may experience significant discomfort.

Severe: The adverse event makes it impossible to perform routine activities. The patient may experience intolerable discomfort or pain.

Classification of causality

Unrelated, possibly related, probably related, definitely related; cannot be assessed, for instance due to lack of information.

Unexpected adverse reaction (UAR) definition (EU Directive 2001/20/EC of 4 April 2001)

An adverse reaction, the nature or severity of which is not consistent with the applicable product information.

Period of observation of adverse events

This is the period between the informed consent and the final examination on day 28.

Documentation of adverse events and serious adverse events

All adverse and serious adverse events will be recorded on specific forms. The adverse event form contains a detailed description of the adverse event (event, beginning and duration, severity, outcome, causality to the study medication, specific therapy), serious adverse event (yes/no), and date and signature of the attending physician.

For serious adverse events (SAEs) a description of the SAE and consequences for the trial are documented.

Reporting of serious adverse events

Serious adverse events have to be reported by the attending physician to one of the principal investigators within 24 hours or not later than the next working day. The SAE is reported to both of independent Ethic Committees (Heidelberg and Burkina Faso).

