## MB in the treatment of malaria

MB (Methylthioniniumchlorid) is a water-soluble dye used for a very long time in industry and medicine. In medicine, it can be administered both orally and parenterally. In humans, the drug is rapidly and widely distributed throughout the body (DiSanto and Wagner 1972). It is generally crossing the blood-brain barrier, but according to animal data i. v. administration initially seems to lead to much higher concentrations in the central nervous system than oral administration (Peter et al. 2000). The drug is well absorbed from the gastrointestinal tract, maximal plasma concentrations are reached after 1-2 hours following oral administration, and the plasma half-life is around 10-12h hours (own unpublished data). Renal excretion of MB is the main elimination pathway: 53-97% of an oral dose is excreted in unchanged or leuco-form in the urine over a 5 day period (DiSanto and Wagner 1972, Peter et al. 2000). In sheep, the 24 hours LD50 after a single i. v. MB administration was 42.3 mg/kg (95% CI: 37.3-47.9); methaemoglobin production was minimal with doses as high as 50 mg/kg, and no significant haematological changes were seen up to 4 weeks after a total dose of 30 mg/kg was administered i. v. over 18 hours (Burrows 1984). From this study it was concluded that the dosage of i. v. MB may safely be increased up to at least 15 mg/kg in the therapy of severe methaemoglobinaemia in humans. However, in one older publication i. v. doses of MB exceeding 7 mg/kg have been reported to cause distressing symptoms, such as restlessness, fine tremor, nausea and chest pain. Grayish blue discolouration of the skin, resembling cyanosis, but with normal values for pO2, and haemolytic anaemia was observed if i. v. doses of 15 mg/kg or more were given to children (Goluboff and Wheaton 1961). In these case reports no significant methaemoglobinaemia was observed. However, MB was well tolerated in oral doses of up to 17 g (5 x 100-200 mg per day) during initial observations in malaria therapy in adults (Guttmann and Ehrlich 1891). Moreover, no significant side effects besides some mild dysuria were reported during treatment of 40 young children, including infants, with malaria in Brasil with oral doses of 20-50 mg/kg/day MB over several days to weeks (Ferreira 1893). It thus appears as if MB given orally is safe even in higher doses compared to intravenous application. This idea is supported by some evidence for significant differences in organ distribution leading to major differences in pharmacokinetics between oral and intravenous MB administration (Peter et al. 2000). Finally, all persons taking MB develop blue urine over the following days.

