Therefore the ideal partner drug to MB still needs to be identified. Two studies have recently shown a synergistic effect of the drugs MB and AS in vitro and in rhesus monkeys (Akoachere et al. 2005, Barker et al. 2005). As both drugs are short acting and no resistance has been demonstrated so far, AS-MB appears to be a promising drug combination. However, to be useful under real life conditions in SSA such a combination needs to be highly effective in a three days regimen. Monotherapy with AS for three days achieved only low cure rates (between 20% and 50% on day 28) in nonimmune populations outside SSA (Borrmann 2003). However, only few studies have studied the efficacy of shorter regimens of AS monotherapy in SSA. While five day regimens of AS monotherapy reached rather high cure rates in semiimmune populations of Tanzania and Nigeria, a three days regimen conducted in 50 children aged 4-15 years with uncomplicated malaria in a hyperendemic area of Gabon had cured only 72% of children by day 28 (Borrmann 2003). However, in this study, the day 14 cure rate was still 92% and children developed mainly asymptomatic parasitaemia afterwards.

AQ alone has been shown to be still sufficiently effective in many areas of SSA where chloroquine is failing (Müller et al. 1996, Greenwood et al. 2005). The combination of AS-AQ has been shown to be highly effective in SSA (International Artemisinin Study Group 2002). AS-AQ together with artemether-lumefantrine have been chosen as the two new official first-line treatments of uncomplicated malaria in Burkina Faso since the year 2006. Thus, comparing the two MB-based combinations MB-AS and MB-AQ with the standard of care AS-AQ is important to judge the safety of these regimens in Burkina Faso and to provide first data on the comparable efficacy.

With effect of May 2006, the World Health Organisation has officially recommended to no longer using malaria monotherapy in the treatment of uncomplicated falciparum malaria (Nelson 2006).

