# Definition of outcomes

Primary endpoint:

- Incidence of observed and self-reported non-serious adverse events over the 28 days observation period (definition chapter 11)

Secondary endpoints:

- Incidence of serious adverse events (definition: chapter 11) over the 28 days observation period
- ACPR rate until D28
- Early treatment failure (ETF) rate
- Late clinical failure (LCF) rate at D14 and D28
- Late parasitological failure (LPF) rate at D14 and D28
- Fever clearance time
- Parasite clearance time
- Change in haematocrit after 2, 3, 7, 14 and 28 days compared to baseline

*Justification:* SAE rates and clinical and parasitological failure rates as well as fever and parasite clearance times are standard endpoints to judge the safety and efficacy of antimalarial drugs. This information will be relevant to plan future phase III trials.

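### The primary adverse-event proportion also counts febrile malaria recurrence to day 28, so the MB-AS safety comparison is mixed with duration of antimalarial protection

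*Protocol*

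**What the plan says.** All places are in the Protocol.

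- *Assessment of secondary endpoints*, AE definition: an adverse event is "any sign, symptom, syndrome, illness that appears or worsens in a subject during the period of observation in the clinical trial". A further clause limits this to events that could affect the child's well-being. On tests: "The term also covers laboratory findings or results of other diagnostic procedures that are considered to be clinically relevant". The definition requires no causal link with the study drug. The observation period ends at the day 28 examination.
- *Definition of outcomes*: the primary endpoint is "Incidence of observed and self-reported non-serious adverse events over the 28 days observation period".
- *Assessment of primary endpoint*: the parameter is "Number and proportion of patients with at least one observed or self-reported adverse event".
- *Definitions*: blue urine is the only event singled out, and events after the start of treatment are tabulated. Parasitaemia with fever from D4 to D28 is late clinical failure (LCF). Parasitaemia without fever from D7 to D28 is late parasitological failure (LPF). Both feed secondary efficacy endpoints.
- *Malaria and malaria control in Africa*: MB and AS are described as short acting, AQ as long-acting. AQ is in MB-AQ and AS-AQ but not in MB-AS.
- *Statistics*: the planning adverse-event rates are 25% (AS-AQ), 25% (MB-AQ) and 5% (MB-AS).

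**The concern.** A child who returns on, say, day 20 with fever and parasites has a new illness that impairs well-being. Under the definition this is an adverse event, and the same episode is an LCF. One episode therefore enters the primary safety endpoint and a secondary efficacy endpoint, and no section says which should hold it.

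The effect need not be equal across arms. The trial runs in the rainy season in an area of high transmission, and MB-AS has no long-acting component. If recurrence before day 28 is more frequent on MB-AS, its adverse-event proportion rises for a reason unrelated to tolerability. The primary objective is to judge the safety of the new combinations for phase III planning, and the sample size assumes that MB-AS has the lowest rate. A tolerability advantage of MB-AS could then be understated. More children would not remove this, because the bias lies in what is counted.

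**Working it through.** **1. The plan's own figure.** For the three-group chi-square test (2 df, 5% level), the noncentrality is λ = 3nV / [p̄(1 − p̄)], where p̄ is the mean of the three rates and V their variance.

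- p̄ = (0.25 + 0.25 + 0.05)/3 = 0.1833.
- V = (2 × 0.0667² + 0.1333²)/3 = 0.00889. Both match *Statistics* (0.183 and 0.009).
- n = 54: λ = 3 × 54 × 0.00889 / (0.1833 × 0.8167) = 9.62, power 79.9%. The stated 80% is reproduced.
- n = 60, the number to be enrolled per arm: λ = 10.69, power 84.2%.

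**2. Effect of counting recurrence.** The protocol gives no recurrence rates by arm, so this step is illustrative. It assumes that the 25/25/5 rates exclude malaria and that recurrence is independent of other events. With d the rate of other adverse events and r the proportion with a recurrence that is counted, the observed rate is 1 − (1 − d)(1 − r). All rows use 60 per arm.

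| Counted recurrence, MB-AS v AQ arms | MB-AS rate | AQ-arm rate | Gap (points) | λ | Global power |
|---|---|---|---|---|---|
| none | 5% | 25% | 20 | 10.69 | 84% |
| 5% v 0% | 1 − 0.95 × 0.95 = 9.8% | 25% | 15.2 | 5.83 | 57% |
| 10% v 2.5% | 1 − 0.95 × 0.90 = 14.5% | 1 − 0.75 × 0.975 = 26.9% | 12.4 | 3.49 | 37% |

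These powers use the approximation that reproduces the plan's 80%. Simulating the chi-square test directly gives about 92%, 61% and 37% for the three rows, so the loss is of the same kind and somewhat larger.

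**3. When would the ranking reverse?** On the same assumptions the gap closes when 0.95(1 − r_MB-AS) = 0.75(1 − r_AQ), that is r_MB-AS = 1 − 0.75(1 − r_AQ)/0.95. For r_AQ = 0%, 5% or 10%, this is 21%, 25% or 29%.

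**The case against.** **All-cause counting is a deliberate and usual choice.** It avoids unblinded judgements of cause, and randomisation keeps the comparison valid for what it counts. That stands, and it is why the all-cause proportion should still be shown. It does not tell a reader whether a difference reflects tolerability or protection.

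**Not every new illness or recurrence counts.** This also stands. The well-being clause limits the definition, the primary endpoint is restricted to non-serious events in *Definition of outcomes*, and afebrile parasitaemia needs a judgement of clinical relevance. In the cited three-day artesunate study (cure 72% by day 28), "the day 14 cure rate was still 92% and children developed mainly asymptomatic parasitaemia afterwards". That study used AS alone in children aged 4-15 years. Its 20-point fall after day 14 is not an estimate of countable recurrence on MB-AS.

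**The planning rates may already include malaria.** *Statistics* does not say. If they do, adding recurrence counts it twice and the power loss in the table does not apply. The mixing of safety and efficacy remains.

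**Two stronger readings are tempting.** A reader might infer that MB-AS will appear less safe than the AQ arms. The documents do not support that. Under the planning rates it needs counted recurrence on MB-AS of about 21 to 29%. Even 20% v 5% gives 1 − 0.95 × 0.80 = 24.0% v 1 − 0.75 × 0.95 = 28.8%, with MB-AS still lowest. A reader might also infer, because for MB "the plasma half-life is around 10-12h hours", that a 28-day window is too long for safety. AQ is long-acting, so a short window would not suit all arms equally, and haematocrit is followed to day 28 in any case.

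**Conclusion.** The point holds in a limited form. As written, the rules place febrile malaria recurrence inside the primary safety proportion as well as among the efficacy failures. The only arm without a long-acting drug is the one likely to be disadvantaged. The supported conclusion is that MB-AS may look less safe than it is relative to the AQ arms. MB-AQ v AS-AQ is largely untouched by this argument, because both contain AQ.

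The size is uncertain. The drop in power from 84% to 57% or 37% rests on three assumptions: planning rates that exclude malaria, independence, and recurrence rates chosen for illustration. The overlap of the two endpoints depends on none of them. It follows from the definitions, which the protocol itself fixes, so it is not a detail left to an analysis plan.

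**What to change.** In the AE definition and the primary endpoint, state that recurrent *P. falciparum* malaria meeting LCF or LPF is reported under the efficacy endpoints and is not counted in the primary non-serious adverse-event proportion. Recurrences that meet a seriousness criterion are reported under the serious adverse event endpoint, in line with the non-serious restriction in *Definition of outcomes*. Report the all-cause proportion, including malaria, beside the primary one.

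The cost is protocol wording and one table. Event onset, temperature and parasitaemia are already collected, so no visit or sample is added. The downside is that a drug-related symptom arising during a recurrence may leave the primary count, but it stays visible in the all-cause table.

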# Statistics

Sample size calculation

When the sample size in each group is 54, a 5% level Chisquare test will have 80% power to detect a difference in proportions by a variance of proportions of 0,009 and an average proportion of 0.183. This szenario is met by the assumption that the rate of adverse events is 25% in the AQ+AS group as well as in the AQ +MB group, and 5% in the AS+MB group.

After a global Chisquare test for the Nullhypothesis "No difference between the three treatment groups" pairwise differences between groups will be tested by two group Chisquare tests. All 4 tests are on the 5% level and no adjustment of the significance level is needed because of the closed testing principle. On closed testing procedures with special reference to ordered analysis of variance. 95% confidence intervals will be calculated for the AE rates. Descriptive statistics will use minimum, 25% quantile, mean, median, 75% quantile, maximum für continuos values and tabulation for categorical values.

# Trial monitoring and auditing

Existence of patients (using the list of expense allowance) and SAEs will be monitored 100%. The informed consents will be checked.

The sponsor is allowed to perform an audit of the investigator site in Nouna. The corresponding documents and data are to be provided by the audited units.

# Ethical and legal aspects

The trial will be conducted in accordance with local laws and the internationally established principles for Good Clinical Practice which have their origin in the Declaration of Helsinki of the World Medical Association (WMA).

Ethics Committee Review

The protocol will be submitted to the ethics committees in Heidelberg and Burkina Faso for review and approval. Protocol amendments will be signed by the PIs and submitted to the ethics committees.

# Documentation and use of trial findings

Data management will be performed at the CRSN in Nouna. Double data entry will be performed. Queries will be formulated and resolved in the CRSN in Nouna in co-operation with the Department of Tropical Hygiene and Public Health, University of Heidelberg.

Statistical advice on analyzing the data will be provided by Prof. [name] (University of Heidelberg) and Prof. [name] (LMU University of Munich).

# Trial duration and dates

The study will be implemented between July and October 2006. Training of field staff and pilot testing of methods will take place 4 weeks before the start of the study.

Early termination of the trial

Reasons that may require the termination of the trial include the following: (1) Incidence of adverse events indicates a potential health hazard caused by the study treatment. (2) It appears that participant’s enrolment or study logistics are unsatisfactory. (3) External evidence that makes it necessary to terminate the trial.

